# Title

**Apollon**

## Title of the research project

Clinical outcome and Quality of Life of multimodal treatment of arteriovenous malformations of the body

## German Clinical Trials Register

DRKS00021019

# Project rationale

## Background and state of the art

Even in the presence of increasing awareness of rare or ‘orphan’ diseases, congenital vascular anomalies of the body remain a diagnostic and therapeutic challenge. Until now, no reliable data exists from national and international treatment centers, regarding the number of affected patients.

Congenital vascular anomalies are currently considered to be among the most complex vascular diseases. They include vascular tumors, based on endothelial cell proliferation, and vascular malformations with underlying mesenchymal and angiogenetic dysplasia^1,2^. Whereas vascular tumors may regress with patient´s age^3^, vascular malformations never regress on their own, but frequently increase in size^4^. They are subdivided in capillary, venous, lymphatic, arterio-venous and combined malformations, depending on the dominant vessel type^5^. According to their appearance, venous malformations are the most common representatives of vascular anomalies (70%), followed by lymphatic malformations (12%), arterio-venous malformations (8%), combined malformation syndromes (6%) and capillary malformations (4%)^5^. Vascular anomalies present with diverse symptoms and morphology which makes the correct clinical diagnosis challenging. The existing various terminologies and classification attempts have been hampering correct diagnostic and therapeutic management in the past^6^. A comprehensive and well-founded global classification system for congenital vascular anomalies is required to allow precise diagnosis and avoid inappropriate therapeutic decisions, especially in rare and multifaceted diseases involving various organ systems. In 2018, the International Society for the Study of Vascular Anomalies (ISSVA) last updated the existing classification and published a supplemented version with insights of vascular anomalies and causal genetic disorders of disease manifestation (https://www.issva.org/UserFiles/file/ISSVA-Classification-2018.pdf).

Vascular malformations, based on an angiogenetic and vasculogenetic dysplastic disorder, are always present at birth (even if asymptomatic) and never regress spontaneously. They may be quiescent for a long time, before mechanical or hormonal influence stimulates them to gain volume and size. With increasing size, vascular malformations can create pain and functional impairment which require therapy. Diagnosis has to address morphology, lesion extent, dominant vessel type and potential complications regarding dermal, orthopedic, neurological and organ manifestations of the lesion. Vascular malformations can be composed of a single vessel type, combined vascular components and malformations with additional non-vascular anomalies and are therefore classified as “simple” or “combined vascular malformations” as well as “vascular malformations associated with other anomalies”. Arterio-venous malformations (AVMs) are rare vascular anomalies, but undoubtedly, the most challenging to treat successfully. As they invariably progress due to the fast flow through the arteriovenous shunts, AVMs can cause various complications, ranging from local pain and discomfort to peripheral ischemia with tissue necrosis, arterial bleeding and in case of long-lasting AV shunting even cardiac failure due to pressure overload^7^. The Schobinger classification for AVMs is valuable for assessing the clinical condition of the vascular anomaly and potential indications to treat^8^. According to Schobinger, four stages are distinguished: stage I (clinical inactive AVM, local skin hyperthermia), stage II (increase of arterio-venous shunting, presence of pulsation and bruit), stage III (destructive AVM, manifestation of ulcerations, bleeding and pain), and stage IV (decompensated AVM, heart insufficiency or cardiac failure). AVMs are fast-flow vascular anomalies. With increasing size, it is increasingly difficult to circumscribe the area of the direct arteriovenous interfaces (“nidus”) of the AVM and to differentiate between feeding inflow arteries and draining outflow veins. Diagnostic imaging provides information on the location, extension, composition and diameter of the feeding and draining vessels to plan for the minimally invasive therapeutic approach to AVMs.

In certain cases AVMs may be associated with hereditary hemorrhagic telangiectasia (HHT), Parkes Weber syndrome (PWS) or Capillary Malformation – AVM syndrome.

AVMs are diagnosed primarily clinical and are subsequently confirmed by cross-sectional imaging such as ultrasound, computed tomography (CT) and Magnetic Resonance Imaging (MRI). Analysis of flow patterns is useful to establish the diagnosis of a fast-flow malformation^9^. Conventional intraarterial arteriography is generally performed immediately before interventional treatment. As arteriovenous malformations frequently penetrate various tissues and as recurrence rates after surgery are high, primary surgical resection has become less common. Nowadays the value of surgery lies in resection of previously embolized lesions that are not or only residually perfused, to manage complications following embolization as well as to reconstruct larger defects occurring after embolization^10^.

Once the decision for invasive treatment is made, complete closure of the AVM is the goal^11^. Incomplete embolization can result in a rapid increase of the lesion. First data in cerebral AVMs indicate that partial embolization results in a release of various angiogenic growth factors from the AVM which foster a progress of the lesion rather than regression^12-14^. The most important therapy approaches are summarized below.

### Conservative therapy: Compression garments can improve symptoms and quality of life. Management of chronic pain should be optimized by a pain specialist. At present, the use of mTOR inhibitors for the treatment of aggressive AVMs is less promising^15^. Novel biologicals targeting the effects of characteristic mutations in AVMs such as PIK3CA or RAS/MAPK may become pharmaceutical options in the future (Venot Q et al Nature 2018, Al-Olabi JCI 2018).

### Embolotherapy: Invasive therapy is indicated in patients with progressive symptoms according to the Schobinger classification. Historically, open surgical ligation and resection of the nidus had been considered the treatment of choice. However, embolization offers a less invasive way of treatment with lower morbidity and acceptable results. In some cases preoperative embolization is an option when complete surgical resection of the nidus is achievable thereafter.

The goal of endovascular embolotherapy is to occlude the nidus or fistulas completely. Commonly used agents are ethanol, N-butyl cyanoacrylate (NBCA) and ethylene-vinyl-alcohol-copolymer (EVOH). Additionally, coils or vascular plugs are needed in some cases, but those only occlude the feeding vessels and never reach the actual nidus, therefore the use is considered as adjuvant, mere coiling of AMVs is nowadays obsolete. Many authors use a combination of the following embolic agents for the endovascular treatment of complex fast-flow malformations.

- *Ethanol.* If injected in the right manner, ethanol is a very potent embolic agent for the occlusion of symptomatic fast-flow malformations. However, there is a high risk of tissue necrosis, nerve injury, and even cardiocirculatory arrest. Because of its low viscosity ethanol passes the nidus very quickly centrally into the lung circulation. Therefore, the pulmonary arterial pressure (PAP) should be monitored continuously during ethanol application. PAP above 25mmHg systolic can be found 10 to 15 minutes after application. To avoid side effects many interventionalists administer less than 0.5 ml per kg.
- *N-butyl cyanoacrylate (NBCA):* N-butyl cyanoacrylate (NBCA) and derivatives are liquid adhesive agents that polymerize irreversibly when exposed to blood. To adjust polymerization time and to enable fluoroscopic visibility NBCA is commonly mixed with lipiodol (ratio, 1:1 to 1:5). One major drawback of NBCA is the potential risk of catheter tip adhesion inside the lesion and the passive, flow-directed administration.
- EVOH Ethylene-vinyl-alcohol-copolymer (EVOH). EVOH is a non-adhesive liquid embolic agent mixed with dimethyl sulfoxid (DMSO) and radiopaque tantalum powder (Onyx, Squid). Compared to NBCA, EVOH has a longer casting time, allowing further penetration into the nidus. It can be administered slowly in a controlled fashion under fluoroscopy, ideally using road map techniques. Using the reflux of EVOH as a plug around the catheter tip, a retrograde flow of EVOH into the whole nidus against the blood-flow is possible ("plug and push technique.")^16^. However, EVOH has some disadvantages. The injection is painful and embolization is therefore performed under general anesthesia.
- *Plugs and coils:* Plugs and coils can be used in simple structured AVMs (type I), for example in pulmonary fast-flow malformations. They have also a role as an embolic agent for outflow occlusion (type II lesions).

*Embolization technique in general:* Most frequently access is gained via the transarterial route, transvenous access maybe additionally helpful in complex lesion. Direct puncture of the nidus is suitable in type II and IIIb lesions. Complete occlusion of the nidus should be achieved, but frequently requires multiple therapy sessions. Embolization of remote arteries should in general be avoided.

Surgery: As stated above surgery is predominantly attempted after successful complete or partial embolization^10^. Aim is to remove the bulk of the lesion, decrease the rate of recurrence after embolization as well as to manage complications. Localized lesions may be amenable for primary surgery if infiltration to adjacent tissue is limited. Plastic reconstructive means are especially important in lesions located in the head and neck area.

### Post procedural care: Postprocedural pain should be treated consequently. Close monitoring of the skin and neurovascular assessments are mandatory. After embolization and other invasive approaches surveillance imaging for recurrence is being performed long-term.

## Study Rationale

Owing to the rare incidence of arteriovenous malformations and additionally the heterogeneity of clinical presentations as well as existing therapeutic approaches no evidence currently exists for image-guided embolotherapy, which however is emerging as the primary treatment of choice. Currently no prospective studies exist investigating the technical and clinical outcome, complication rates and therapy-induced changes in health-related quality of life. Due to the limited evidence regarding the outcome of angiographically guided AVM treatment and at the same time the high morbidity of the disease, prospective evidence is urgently needed.

## Risk-benefit-ratio

Minimal-invasive treatment methods for arterio-venous malformations have significantly improved during the last years. The aim of AV malformations therapy is to reduce symptoms, prevent potential impairment of functional tissue and resulting complications and thus help patients to improve their quality of life. An incomplete, non-indexed or incorrect therapy often leads to a worsening of symptoms. A strict risk-benefit assessment is therefore necessary before any invasive therapy.

With advancements in the development of embolic agents and microcatheter techniques, embolization therapy has evolved as the mainstay of treatment for peripheral AVMs. Although less invasive and relatively safe, embolization carries the risk of displacement of embolic material with the risk of systemic and pulmonary embolism, occlusion of non-AVM vasculature with subsequent tissue injury, and systemic reaction to embolic agents. Bleeding and infections are rare but can evolve as severe complications. The risk of exposure to contrast material and ionizing ration is especially important in children and young adults.

Postembolization syndrome caused by tissue necrosis may be encountered after a successful interventional embolization. The symptoms of fever, leukocytosis, pain and nausea occur soon after embolization and typically resolve within a few days. Only close laboratory work-ups and clinical observation can differentiate postembolization syndrome from an infective complication.

The actual frequencies of the complications mentioned above is not known and the existing moderate knowledge is derived from retrospective patient cohorts with low sample size, normally from one center. Thus, there is an urgent need for data from larger cohorts, at best collected in prospective manner and from multiple experienced centers.

The present protocol of an established multimodal therapy concept used in clinical routine in interdisciplinary consensus offers the potential to at the same time reduce morbidity and increase individually the health-related quality of life in patients with AV malformations. In view of the natural progress of the disease, which untreated may lead to peripheral limb necrosis, tissue loss, arterial bleeding, and cardiac failure, the treatment benefits seem to outweigh the associated risks.

The prospective study to assess the clinical outcome, safety and health-related quality of life is expected to generate evidence for minimally-invasive treatment concepts with improved patient selection.

In addition, the multi-centre design of the study with the potential to assess a larger patient population will provide an improved understanding in the dynamics and natural course of this rare disease.

# Study objectives

The study objective is to determine the effectiveness, safety and clinical outcome including health-related Quality of Life of multimodal treatment of arteriovenous malformations. Therapy options include conservative management, medical treatment, minimally-invasive image-guided therapy (sclerotherapy, embolization) and surgery as well as combinations of all of the above. Of note, especially image-guided therapy routinely requires multiple therapy sessions. Clinical outcome shall therefore be assessed before initiation of treatment, during therapy (including in between multiple therapy sessions) as well as at defined time points after therapy of the AV malformation. Therapy assessment is based on the recommendations of the international core outcome set (OVAMA)^17^. Additionally, liquid biopsies are being obtained from peripheral blood to investigate potential biomarkers (cytokines, chemokines, growth factors) for therapy response or/and disease progression.

## Primary study objectives

To determine effectiveness and clinical outcome of AV malformation therapy we will evaluate the self-reported therapy success in form of the changes in overall *patient-reported* health-related Quality of life (QoL) as the primary study objective. In order to investigate the changes in QoL in a standardized way, psychometrically evaluated questionnaires will be used (SF-36v2: adults, SF-10: kids). The SF-36v2 and the SF-10 health survey are internationally approved generic questionnaires to assess subjective health.

## Secondary study objectives

To determine effectiveness and clinical outcome of multimodal treatment of vascular malformations the following points are additionally examined as secondary study objectives (based on OVAMA^17-20^):

- *Physician-reported* signs: general appearance (for example swelling, pulsation, ulceration, cardiovascular health issues, bleeding) and location-specific signs (for example extremity length discrepancy, physical impairment)
- Imaging Response: MR-angiographically measured reduction of the size (volume) of the nidus of the AVM and degree of devascularization, in case of superficial cutaneous lesions patient photographs will be considered additionally
- Concordance between clinical and imaging outcome
- Serum/Plasma levels and respectively change of levels of potential biomarkers for prediction of therapy response or/and disease progression in an exploratory manner
- Recurrence Rate following multimodal AVM treatment
- Other local and systemic side effects at the follow-up visit

Assessments of the points listed above will be conducted at the following time points:

- At time of first presentation to the vascular malformation clinic after inclusion in the study
- In case of conservative management biannually thereafter for 36 months
- Before initiation of interventional/surgical therapy as well as before each cycle of l treatment
- After initiation of interventional/surgical therapy every 6 months
- After completion of interventional/surgical therapy follow-up is performed at 6 (primary endpoint), 12, 24 and 36 months

To determine safety of multimodal treatment of vascular malformations the following points are additionally examined as secondary study objectives:

• Treatment-associated morbidity including temporary (e.g. vascular procedure complication requiring surgical management, local tissue necrosis, infection, bleeding, thrombosis, embolism due to unintended dislocation of the agent to the lung, cardiovascular systemic complications) and permanent sequalae (e. g. motoric and sensory nerve injury, lasting joint movement restrictions) and mortality

• Other acute local and systemic side effects peri- and postinterventional

## Primary Endpoint:

*Patient-reported* health-related Quality of Life in a multimodal therapy concept for AV malformation treatment at 6 months after completion of invasive treatment. In order to investigate the QoL in a standardized way, established questionnaires (SF-36v2, SF-10) will be used.

- Adults: SF-36 Version 2: The SF-36v2 for adults (> 13 years) consists of eight scaled scores, which are the weighted sums of the questions in their section. The eight sections are vitality (VT; feeling energetic, absence of fatigue), physical functioning (PF; extent to which health limits daily physical activities), bodily pain (BP; intensity of pain and effect on activities), general health perception (GH; current health status, health expectations and resistance to illness), physical role functioning (RF; extent to which physical health interfere with typical role functions), emotional role functioning (RE; extent to which emotional health interferes with typical role functions), social functioning (SF; extent to which health-related problems interfere with normal social activities) and mental health (MH; general mental health, including anxiety, depression, positive affects). These eight sections yield two summary measures:
  - physical component summary (PCS)
  - mental component summary (MCS).
- Kids: SF-10: The SF-10 is a 10-item questionnaire for children aged 5 – 13 years designed to measure health-related QoL in children. Unlike the SF-36v2 it should be completed by caregivers. The scoring method yields two summary measures:
  - physical summary score (PHS-10)
  - psychosocial summary score (PSS-10)

## Secondary Endpoints

- Therapeutic efficiency and clinical outcome of the selected therapeutic concept for AV malformation treatment at 12, 24, 36 months after completion of invasive treatment:
- *Physician-reported* signs: general appearance (for example swelling, pulsation, ulceration, cardiovascular health issues, bleeding) and location-specific signs (for example extremity length discrepancy, physical impairment)
- Radiological assessment
  - Evaluation of the therapeutic response depending on imagine outcome:
    - MR-angiographically measured reduction of the size (volume) of the nidus of the AVM
    - Degree of AVM devascularization (modified from Cho et al 2006 and 2008)^21,22^ before treatment to both primary and secondary endpoints:
      - 100% devascularization
      - 76-99% devascularization
      - 50-75% devascularization
      - < 50% devascularization
- Concordance between clinical and imaging outcome
- Changes in patient photographs (only qualitative analysis with Likert scale)
- Identification of potential biomarkers (as of now: Angiopoetin-I, Angiopoetin-II, S-endoglin, TGF-beta, Integrin beta-3, Ephrin-B2, HGF, Angiostatin, Endostatin, Endothelin, bFGF, VEGF, IL-6, PDGF, S100A8/9, S100B, PROX1, NRP2, PIK3CA including circulating free DNA) for prediction of therapy response or/and disease progression in an exploratory manner. For this purpose, an additional blood sample of about 10 ml blood is obtained for the study. In case of a clinically required biopsy of the vascular malformation, obtained material may similarly be assessed for additional tissue biomarkers.
- Recurrence rates:
  - Clinical recurrence (reappearance or aggravation of symptoms or findings which were initially regressive)
  - Imaging recurrence (recurrent increase in size or reperfusion of the vascular malformation after initial regression, occurrence of newly perfused AVM not detected before)
  - Recurrence rates/Progression after initial partial versus after complete response
  - Recurrence rates depending on the kind of treatment, the type of embolic agent (in the case of sclerotherapy, embolization), and the initial clinical findings of vascular malformation (initial size or the initial severity of symptoms)
- Other local and systemic side effects at the follow-up visit

Therapeutic safety of the selected therapeutic concept for AV malformation treatment

- Treatment-associated morbidity including temporary (vascular procedure complication requiring surgical management, local tissue necrosis, infection, bleeding, thrombosis, embolism due to unintended dislocation of the agent to the lung) and permanent sequalae (motoric and sensory nerve injury, lasting joint movement restrictions) and mortality
- Other acute local and systemic side effects

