# Study design

The study is a **multicenter, exploratory, prospective open-label study**. Due to **the multimodal therapy concept**, a comparison of the different therapy approaches will be conducted.

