In case of **surgical resections** of AVM tissue, surgery is performed after complete/near-complete embolization. Surgical resection is similarly performed under general anesthesia. Neuromonitoring will be routinely used in case of proximity of the AVM to major nerve structures. Surgical resection is limited to mass-forming AVM tissue, complete resection of the entire malformation is rarely possible and not goal of the procedure.

Peripheral venous blood samples will be obtained on the day before, on day 1 and 3 following embolization as well during follow up at the same time points of health related QoL assessment. Blood samples will be processes and subsequently frozen until subsequent biomarker analysis.

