# Statistics

Analysis of clinical patient data, QoL data and Biomarkeranalysis will be performed separated from each other in a blinded setting. The study has an exploratory focus. All statistical testing will be performed based on a significance level of α=5%. No adjustment for multiple testing is planned.

Standard descriptive statistics will be used when reporting the study data. For continuous data, distribution parameters (mean, standard deviation, minimum, median, and maximum) will be computed and for categorical data, frequency counts will be given. If needed, 95% confidence intervals will be specified.

For the primary study parameters (scores PCS and MCS from adult SF-36v2 quality of life questionnaires, as well as PHS and PSS from kids SF-10 questionnaires), paired t-tests will be calculated comparing the scores at baseline to the respective scores at 6 months after the end of treatment (for embolized patients) or at the 24 months FU (for patients with conservative or medical treatment).

All QoL scores and subscores, as well as patient and physician reported pain and symptom data will be tabulated by study visit. Where appropriate, such data will also be summarized for different patient subgroups (e.g., age group, Schobinger stage, study treatment, etc.)

Morbidity, Mortality, and recurrence rates will be compared for different patient subgroups using Chi Square or Fisher’s exact test.

Summary statistics for AVM nidus volume reduction will be presented stratified by clinical outcome, as well as by patient subgroups, as needed. Crosstabulations of AVM devascularization (100% / 76-99% /50-75% / < 50% devascularization) vs. different clinical outcomes will be presented.

A sample size of N=74 (for children and adults, respectively) achieves 80% power to detect a mean of paired differences of 5 with an estimated standard deviation of differences of 15 and with a significance level (alpha) of 0,05 using a two-sided paired t-test.

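### The unadjusted comparison of recurrence by kind of treatment is confounded by embolization response, because resection follows complete or near-complete embolization; the direction of the bias depends on who counts as at risk

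*Protocol*

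**What the plan says.** - **Study design** announces that "a comparison of the different therapy approaches will be conducted". There is no randomisation.
- **Secondary Endpoints** lists "Recurrence rates depending on the kind of treatment, the type of embolic agent", together with initial clinical findings. Partial versus complete response is a separate recurrence item and is not crossed with kind of treatment.
- **Secondary Endpoints** also defines recurrence. Clinical recurrence needs an earlier improvement. Imaging recurrence needs an earlier regression, except that newly perfused malformation also counts.
- **Statistics** fixes the method: "recurrence rates will be compared for different patient subgroups using Chi Square or Fisher’s exact test". No stratification, restriction or adjustment is named.
- **Description of the procedures** states, for resection of malformation tissue, that "surgery is performed after complete/near-complete embolization". It limits resection to mass-forming tissue.
- **Background and state of the art** warns that "Incomplete embolization can result in a rapid increase of the lesion". Its paragraph on surgery is wider than the procedures section: "As stated above surgery is predominantly attempted after successful complete or partial embolization", and "Localized lesions may be amenable for primary surgery if infiltration to adjacent tissue is limited". The same paragraph gives reducing recurrence after embolization as one aim of surgery.

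**The concern.** Under the procedures section, a good embolization result comes before resection. Among embolized patients, the operated group then holds good responders only. The non-operated group holds the remaining good responders plus the incomplete embolizations. A crude test between the two mixes any effect of surgery with the effect of embolization response, which the Protocol's background treats as prognostic.

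The selection happens after treatment has started. Adjusting for size or severity at inclusion would therefore not remove it. This is more specific than the general caution that treatment was not randomised, because the treatment sequence itself creates the imbalance.

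The Protocol's rationale says that no prospective evidence exists and names lower recurrence as an aim of surgery. A crude difference in either direction could therefore be read as evidence about surgery when it reflects who was eligible for it.

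**Working it through.** **Inputs from the Protocol.** Total sample 148; two-sided 5% level; unadjusted chi-square or Fisher test; surgery after complete or near-complete embolization. The only sample-size calculation is for the paired t-test on quality of life: N=74 per age group, difference 5, SD 15. It reproduces (73 patients suffice; 74 give 80.8% power) but says nothing about recurrence.

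**Assumed inputs (none in the Protocol).** N = 110 embolized patients; q = 0.6 reach complete or near-complete embolization; s = 0.5 of those are operated; recurrence rc = 20% after complete or near-complete embolization; rp after incomplete embolization is varied. Surgery has no effect.

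**Formulas.**
- Operated group: expected recurrence = rc.
- Embolization-only group: [q(1−s)·rc + (1−q)·rp] / [q(1−s) + (1−q)].

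**Expected group sizes.** Operated: 110 × 0.6 × 0.5 = 33. Not operated: 33 good responders + 44 incomplete = 77.

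**Results with no surgery effect** (chi-square at 5%, simulated):

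| rp | With surgery | Embolization only | Ratio | False rejection |
|---|---|---|---|---|
| 50% | 20% | (6.6 + 22.0)/77 = 37.1% | 0.54 | about 42% |
| 40% | 20% | (6.6 + 17.6)/77 = 31.4% | 0.64 | about 22% |
| 20% | 20% | (6.6 + 8.8)/77 = 20.0% | 1.00 | about 5% |
| 0% | 20% | (6.6 + 0)/77 = 8.6% | 2.33 | about 40%, against surgery |

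Fisher's test gives somewhat lower figures: about 37–38% in the first row and 19–20% in the second.

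The last row represents lesions that never regressed. They stay in the denominator, but under the Protocol's definition they largely cannot recur.

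**Sensitivity to q and s** (N = 110, rc = 20%, rp = 40%). With q = 0.8 and s = 0.5: 20% against 26.7%, false rejection about 12%. With q = 0.8 and s = 0.2: 20% against 24.8%, false rejection about 5–6%, close to nominal.

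**Wider grid** (all 148 embolized, q = 0.4–0.8, s = 0.3–0.5, Fisher's test). With rp of 40–60%, the spurious ratio is 0.40–0.79 and false rejection is about 8–83%, nearly all in favour of surgery. With rp of 0–10%, the ratio is 1.15–4.00, against surgery.

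**After restriction** to complete or near-complete embolization, both groups have 20% expected recurrence. In the N = 110 scenarios, false rejection is about 5% with chi-square and 3–4% with Fisher's test.

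**The case against.** A reader might infer that surgery is bound to look protective and that the trial would probably report such a benefit. The documents do not support this. Recurrence is defined mainly as a return after improvement, so an embolization that never worked may be uncountable, and the bias can then run against surgery. The Protocol adds progression only to the partial-versus-complete item, not to the kind-of-treatment item. The background warning about rapid growth describes progression and gives no recurrence rate. Even under the assumptions that favour surgery at N = 110, false significance arises in 22–42% of trials, which is less than half.

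Other objections stand in part:
- **Surgery is not described uniformly.** The background also allows surgery after partial embolization and primary surgery. Such exceptions would dilute the selection but not remove it.
- **Repeated sessions aim at complete or near-complete occlusion.** The share of incomplete embolizations may be small, and the bias would then be small, as the sensitivity runs show.
- **The exact contrast is not spelled out.** The Protocol says kind of treatment and patient subgroups, and a statistical analysis plan that is not shown may define the groups. However, the Protocol already names the unadjusted test and does not cross response with treatment.
- **Resection is limited to mass-forming tissue.** This is a further selection of unknown direction, and stratifying by response does not remove it.
- **The study is declared exploratory and the endpoint is secondary.** This limits the weight of the point but does not make the crude test interpretable.

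**Conclusion.** The point holds without a fixed direction. With resection placed after complete or near-complete embolization, a crude comparison of recurrence between operated and non-operated embolized patients is biased when surgery has no effect, unless recurrence is the same in both response groups.

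If incompletely embolized lesions recur or progress more often, the bias favours surgery. If lesions that never regressed stay in the denominator but cannot recur, it goes against surgery. Every rate behind the sizes shown is assumed, so they illustrate the problem and do not predict this trial's result. At high rates of near-complete embolization with few patients operated, the false-positive rate is close to nominal.

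Severity is minor to moderate.

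**What to change.** In Statistics, replace the crude comparison for surgery with the following:

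1. Compare embolization plus surgery with embolization alone within strata of the existing devascularization grade. State which grades count as complete or near-complete (100% and 76–99% would be the natural reading), since the Protocol does not map the term to its four grades. Take the grade from the last imaging after embolization and before any surgery.
2. Limit the recurrence denominator to patients with initial regression.
3. Use one start of follow-up, defined the same way in both groups. Completion of treatment fits the existing visit schedule. A surgery decision date would not work, because patients who never have surgery do not have one.
4. Report partial responders separately, with progression as well as recurrence.
5. Label the comparison non-randomised and descriptive.

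The background paragraph on surgery and the procedures section should also be reconciled on when surgery is done, because the group definitions depend on it.

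**Cost.** Imaging response is already to be assessed before each treatment cycle, so the main work is wording plus recording the grade at the pre-surgery imaging. The comparison uses fewer patients. In the example with 20% recurrence in each group, 33 against 33 gives a 95% half-width of 1.96 × √(0.16/33 + 0.16/33) = 19.3 percentage points, compared with 1.96 × √(0.16/33 + 0.16/77) = 16.3 points for 33 against 77. Selection by indication within strata remains.
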